#### Data collection methods and data management

Home care nurses and practical nurses conduct clinical tests and DRP-RAT –assessments, compile medication lists and deliver the data to the research coordinator (TT). Pharmacists use case report form in medication reviews and research coordinator receives the data. Data are entered into a computerized database by the research coordinator. All patients will be given a unique study number to preserve confidentiality. The collected data will be verified for accuracy, missing data, and data consistency with the documents source (medication lists, clinical test forms).

#### Statistical methods

Data will be analyzed on an intention to treat principle, including all randomized participants in the group to which they were randomly assigned. Also per protocol analysis to compare participants from intervention group with clinically significant medication changes conducted due to CMR, MR or PR, with control group will be performed.

The effectiveness of intervention compared to controls receiving standard home care will be first analyzed with unadjusted analysis. If there exists any group differences in participant characteristics or clinical outcomes at baseline, these variables will be included in adjusted analysis.

Descriptive statistics (mean, median or percentages as appropriate) will be used to summarize the participant characteristics and clinical outcomes. The comparison in the participant characteristics and clinical outcomes at baseline between groups will be done by two-sample t-test for normally distributed variables and by Mann-Whitney U-test for non-normally distributed variables. Chi-square test will be used for categorical variables.

Continuous outcomes will be analyzed with analysis of variance or covariance and repeated measures analysis of variance or covariance. Dichotomous outcomes will be analyzed by binary logistic regression and ordinal outcomes by cumulative logistic regression using generalized estimating equations to account for the correlation between the repeated measurements. Participants with baseline measurement and at least one follow-up measurement will be included in longitudinal analysis. Two-sided statistical tests with a 5% level of significance will be used.

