### Description of developed CoMM for home care clients (intervention)

The developed CoMM consists of five main stages in which clinically significant DRPs can be identified and solved using collaborative procedures and medication reviews (Fig. 3, Table 1). PNs were trained to observe potential medication risks on routine home visits more systematically than before and to report detected clinically significant DRPs to the coordinating pharmacist (Fig. 3: Stage I: Risk Assessment). The coordinating pharmacist prepared the cases for the triage meeting (Fig. 3: Stages I and II), in which the leading home care physician and the coordinating pharmacist decided on further actions for clients with clinically significant DRPs (50–70 cases per triage meeting of two hours). The actions included more comprehensive medication reviews according to the needs of the clients involving their own physicians and nurses/PNs. In most complicated cases also home visit and the client’s clinical interview were conducted (Fig. 3: Stage III). Based on the information gathered in Stages I-III client’s personal physician made decisions on required actions (Fig. 3: Stage IV) and follow-up was organized (Fig. 3: Stage V).

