#### Randomization

Participants were randomized to an intervention group (IG) and a control group (CG) receiving standard home care. To prevent contamination between IG and CG and subsequent dilution of the intervention, participants were randomized by home care areas (2 areas to the IG, 3 areas to the CG) since each home care area has its own nursing staff. The randomization was performed by sealed envelopes. The study is considered as open-label. The IG (*n* = 104) received the intervention (CoMM) during the first year, while the CG (*n* = 87) received standard care and received the same intervention after the first year (delayed intervention as control).

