#### Sample size

The study sample was all home care clients, meeting inclusion criteria and giving voluntary informed consent, in the Lohja Home Care Unit due to the practical, administrative and financial issues. Sample size calculations were not performed.

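### The analysis labelled per protocol keeps only intervention clients whose medication was changed and compares them with all controls, so it is biased by selection and should be descriptive only

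*Protocol article*

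**What the plan says.** The Statistical methods section of the protocol article puts intention to treat first: "Data will be analyzed on an intention to treat principle, including all randomized participants in the group to which they were randomly assigned". It then adds a "per protocol analysis to compare participants from intervention group with clinically significant medication changes conducted due to CMR, MR or PR, with control group". No matching restriction is placed on the controls.

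The same section says treatment comparisons are first made unadjusted, and that variables differing between groups at baseline then enter an adjusted analysis. Covariance models are named for continuous outcomes. On error rate it says: "Two-sided statistical tests with a 5% level of significance will be used".

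How a client comes to have a qualifying change is described elsewhere. The account of how the model was developed says that reviews are allocated by severity of the drug-related problems. In the description of the intervention, at triage "the leading home care physician and the coordinating pharmacist decided on further actions for clients with clinically significant DRPs", and the client's own physician makes the final decision. The Harms section confirms that medication changes follow the physicians' normal clinical practice.

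**The concern.** A per-protocol set should contain those who received the trial procedure as planned. Here the procedure is a five-stage process of risk assessment, triage, review where needed, physician decision and follow-up. A client who was assessed and correctly judged to need no change followed it fully, yet is excluded. The set is defined by what the process produced, not by adherence to it.

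Retained clients are expected to have more serious drug-related problems than the intervention group as a whole, and a physician who agreed to act. The other side of the comparison is unselected: in the first year "the CG (*n* = 87) received standard care", so no control can have a change due to one of the model's reviews. After the first year controls receive the model too, but the restriction as written still applies to the intervention group alone.

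The two sides would thus differ without any treatment effect. On follow-up levels the selected clients tend to look worse. On change from baseline they tend to look better, through regression to the mean. For medication and DRP outcomes there is a further overlap: DRP-RAT, SFINX and Salko findings feed triage and are also outcome measures, and the selection event is itself a change in medication.

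**Working it through.** The plan has no power or effect-size figure to reproduce ("Sample size calculations were not performed"). The figure at stake is the nominal two-sided 5% level.

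**Inputs from the protocol (Randomization, Statistical methods):** 104 intervention clients, 87 controls, 5% two-sided.

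**Assumptions, not in the protocol:** a fraction f of intervention clients has a qualifying change; baseline and follow-up correlate r; the selection score correlates ρ with the measured baseline or with underlying severity. There is no treatment effect. Clients are treated as independent, ignoring clustering by area, to isolate the effect of selection.

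**1. Shift from selection.** With f = 0.40, 42 clients are kept. The mean of the top fraction of a standard normal score is k = φ(z)/f with z = z(1−f), so k = 0.966. The standard error of a difference, in SD units, is √(1/42 + 1/87) = 0.188.

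**2. Unadjusted follow-up level, selection related to measured baseline, r = 0.6.** Bias = r·ρ·k. Rejection = Φ(bias/SE − 1.96) + Φ(−bias/SE − 1.96).

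| ρ | Bias (SD) | Bias/SE | Rejection |
|---|---|---|---|
| 0.3 | 0.6 × 0.3 × 0.966 = +0.17 | 0.93 | 15% |
| 0.5 | +0.29 | 1.54 | 34% |
| 1 | +0.58 | 3.08 | 87% |

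Simulation gives 15%, 33% and 88–89%. The last exceeds the formula because strict ranking also narrows the spread of the selected group.

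**3. Change from baseline, same setting.** Bias = −(1 − r)·ρ·k. The SD of change is √(2(1 − r)) = 0.894, so SE = 0.894 × 0.188 = 0.168.

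| ρ | Bias (SD) | Absolute bias/SE | Rejection |
|---|---|---|---|
| 0.3 | −0.12 | 0.69 | 11% |
| 0.5 | −0.19 | 1.15 | 21% |
| 1 | −0.39 | 2.30 | 63% |

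Simulation agrees. The sign is opposite to step 2.

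**4. Baseline-adjusted ANCOVA.**

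- *Selection depends only on the measured baseline.* In the setting of steps 2 and 3, ANCOVA rejects in about 5% of runs with essentially zero mean bias.
- *Selection follows underlying severity.* Let baseline and follow-up each correlate 0.7 with severity, hence 0.49 with each other. Both shift by 0.7·ρ·k in the selected group, and adjustment removes about 0.49 of that shift. The remainder is about 0.51 × 0.7·ρ·k = 0.357·ρ·k. For f = 0.35 (k = 1.058) and ρ = 0.5 this is 0.19 SD; simulation gives 0.19 SD and 19% rejection. Across f = 20%, 35% and 50%, rejection is 9–11% at ρ = 0.3, 16–21% at ρ = 0.5 and 28–36% at ρ = 0.7. Strict ranking on severity, with f = 0.40 and r = 0.6, gives about 57%.

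**5. Binary medication outcome.** Suppose a fraction q in each arm has a medication change, with outcome probability 0.30 after a change and 0.05 otherwise. The selected group has rate 0.30 and controls have 0.30q + 0.05(1 − q).

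| q | Control rate | Spurious difference (points) | Rejection (simulated) |
|---|---|---|---|
| 20% | 0.100 | 20 | 64% |
| 35% | 0.1375 | 16 | 56% |
| 50% | 0.175 | 12.5 | 40% |

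**6. Checks.** Comparing all 104 with all 87 under the severity model of step 4 and the binary model of step 5 keeps the level: 4.5–5.6% for the continuous outcome and 4.2–5.2% for the binary one. If selection is unrelated to the outcome (ρ = 0), the restricted comparison also stays at 4.5–5.5%.

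**The case against.** The strongest reply is that the section itself plans adjustment for variables that differ at baseline. In the simulations where selection acts only through the measured baseline, that adjustment removes the bias completely. A reader might infer from the 88–89% and 63% figures that these are the error rates of the planned analysis. They are not: they belong to unadjusted tests under strict ranking, which the protocol does not describe. Severity guides who is reviewed, but qualifying changes may also come from prescription review, the least detailed level, and each depends on an individual physician.

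This reply stands in part. The unadjusted result would still be produced, and produced first. The protocol does not say that the baseline check is repeated within the selected set. And selection also draws on symptoms, laboratory results, interviews and clinical judgement, which adjustment for measured baseline variables need not capture; that is the 9–36% case.

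A second reply is that the analysis is supplementary. That stands. A reader might infer that the trial's main result is compromised, but intention to treat comes first and does not use this set. Nor does the protocol claim that the comparison estimates the effect in treated clients, although the label invites that reading.

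**Conclusion.** The point holds as a defect of definition and labelling in a supplementary analysis. It should be fixed, but it does not threaten the main inference. The comparison selects on a post-randomisation result of the intervention, in one arm, by a route that the protocol ties to severity and physician decision.

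Its false-positive rate ranges from about 5%, when selection acts only through an adjusted baseline, through roughly 9–36% when selection also reflects underlying severity, to much higher values for unadjusted tests or strict ranking. These sizes rest on assumed selected fractions, correlations and outcome rates. What does not rest on them is that the set is not a per-protocol set and that the bias can run for or against the intervention depending on the outcome and how it is analysed.

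**What to change.** Remove the per-protocol label and any inferential use of this comparison. Report intervention clients with a qualifying medication change descriptively, without a test against controls.

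If a targeted estimate is wanted, define the subgroup at baseline by one rule in both arms: clients who screen positive on DRP-RAT, SFINX or Salko. Compare intervention with control as randomised by area, and always adjust for baseline rather than only when a difference is seen. First confirm that these baseline data exist for controls. The measurement schedule makes this plausible, but the protocol does not state it explicitly for that group.

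An instrumental-variable estimate with area allocation as instrument is not a good substitute. Nurse training, reconciliation, risk assessment and follow-up could affect outcomes without a qualifying change, so the exclusion restriction is doubtful, and the instrument varies over only five areas.

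The cost is a change of wording, with no new measurements if the control baseline data are there. The drawback is a less striking and less precise subgroup estimate that answers a slightly different question: the effect in clients with detectable problems at baseline, not in those whose medication was changed.

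### Adjustment variables are chosen by whether the groups differ at baseline, so the covariate set is data-dependent and usually omits the outcome's own baseline value

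*Protocol article*

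**What the plan says.** All of the relevant text is in the protocol article, mostly under Statistical methods.

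- **Order of analysis.** Effectiveness "will be first analyzed with unadjusted analysis".
- **Rule for covariates.** "If there exists any group differences in participant characteristics or clinical outcomes at baseline, these variables will be included in adjusted analysis". No covariate is named in advance.
- **How groups are compared at baseline.** "The comparison in the participant characteristics and clinical outcomes at baseline between groups will be done by two-sample t-test for normally distributed variables", with Mann-Whitney for non-normal variables and chi-square for categorical ones. These are client-level tests.
- **Significance level.** "Two-sided statistical tests with a 5% level of significance will be used". The sentence is general; it is not attached to the covariate rule.
- **Outcome models.** "Continuous outcomes will be analyzed with analysis of variance or covariance and repeated measures analysis of variance or covariance". Logistic models with generalized estimating equations are planned for dichotomous and ordinal outcomes.
- **Longitudinal set.** "Participants with baseline measurement and at least one follow-up measurement will be included in longitudinal analysis".

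Under Randomization, five home care areas were allocated, two to intervention and three to control, giving 104 and 87 clients.

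**The concern.** Selecting covariates by baseline comparison answers the wrong question. Adjustment is worth making for a variable that predicts the outcome. The baseline value of the outcome is usually the best such variable, and it brings most of its benefit even when the arms look alike. A baseline test measures only how far apart the arms happen to be.

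Three consequences follow if the rule is applied as written.

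1. An imbalance too small to be flagged stays in the comparison, even on a strongly prognostic variable.
2. The gain in precision from the baseline score is forgone whenever no difference is found. This matters because, under Sample size, the article says that no calculation was made, so adequate precision cannot be presumed.
3. The covariate set is known only after the data are seen and can differ from one outcome to the next. The article names many primary measures and does not say whether the unadjusted or the adjusted result decides, so the choice is not innocuous.

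**Working it through.** The article gives no power, effect size or SD, so there is no stated figure to reproduce. The only check available is 104 + 87 = 191, which agrees with the number of consented clients in the Abstract.

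**Inputs from the article:** group sizes 104 and 87; two-sided 5% tests.

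**Assumptions not in the article:** a difference means p<0.05; baseline/follow-up correlation r between 0.5 and 0.7; equal SD at baseline and follow-up; for power, a true effect of 0.3 SD. Clients are treated as independent unless stated otherwise.

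**Step 1: the largest imbalance that escapes the rule.** The standard error of a baseline difference is sqrt(1/104 + 1/87) = 0.1453 SD. The limit is 1.96 × 0.1453 = 0.285 SD.

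**Step 2: what such an imbalance does.** In an unadjusted comparison of follow-up values, a baseline gap d shifts the expected difference by r × d.
- r = 0.5: 0.5 × 0.285 = 0.14 SD
- r = 0.7: 0.7 × 0.285 = 0.20 SD

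These are values at the limit, given that such a gap has occurred. They are not average biases.

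**Step 3: how often the baseline score enters.** With independent clients and random allocation, a 5% test flags it in about 5% of trials. Simulation of 5,000 trials per setting gave 4.1% to 5.4%.

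**Step 4: the precision lost.** Adjusting a continuous outcome for baseline multiplies the residual variance by 1 − r², a cut of 0.5² = 25% or 0.7² = 49%. The effect detectable with 80% power is (1.96 + 0.84) × 0.1453 × sqrt(1 − r²).

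| Analysis | Detectable effect, r = 0.5 | Detectable effect, r = 0.7 | Power at 0.3 SD, r = 0.5 | Power at 0.3 SD, r = 0.7 |
|---|---|---|---|---|
| Unadjusted | 0.41 SD | 0.41 SD | 0.54 | 0.54 |
| Baseline always included | 0.35 SD | 0.29 SD | 0.66 | 0.82 |
| Rule as written (simulated) | not computed | not computed | 0.54 | 0.55 |

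Simulation of the always-adjusted analysis gave 0.65 and 0.82, in line with the formula. The rule performs almost like no adjustment at all.

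**Step 5: how stable the covariate set is.** Table 1 lists eight clinical tests. With eight independent baseline tests the chance of at least one false flag is 1 − 0.95^8 = 34%. With 10 it is 40% and with 20 it is 64%. Correlated measures would change these figures.

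**Step 6: the same rule with areas as clusters.** With areas of equal size within each arm (assumed), the client-level baseline test flags a score in about 14% to 15% of trials at an assumed intraclass correlation of 0.02, and in 25% to 26% at 0.05. Clustering therefore makes inclusion more frequent, though the score is still left out in most trials.

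**The case against.** **The rule acts when it matters most for bias.** A reader might infer that baseline scores are left out just when they are most useful, or that imbalances between areas go uncorrected. The article supports neither reading. A large measured imbalance is flagged and enters the adjusted analysis, and Step 6 shows that imbalance between areas makes flagging more likely. Put as numbers: at an assumed intraclass correlation of 0.05 and equal area sizes, the variance of a baseline difference is 0.05 × (1/2 + 1/3) + 0.95 × 0.0211 = 0.0617, so its SE is 0.248 SD. The chance of a gap above 0.2 SD is then about 42%, but about 25 of those 42 percentage points lie above 0.285 SD and would be adjusted for. About 17 points remain. This objection stands. What the rule loses is mainly precision, plus sub-threshold imbalance.

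**Baseline may already be in some models.** The section names analysis of covariance and repeated-measures models, and the longitudinal set requires a baseline value. If baseline is a time point, a group-by-time contrast uses it, and the shift in Step 2 would differ in size and direction. This stands as a limit: omission is not certain for every analysis. Still, no sentence makes the baseline score a standing covariate, and the quoted sentence is the only inclusion rule.

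**The cut-off is inferred.** This is true. But a judgement of difference without a cut-off would be more dependent on the data, not less.

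**The covariate list belongs in an analysis plan.** A full list may well be there, and its absence here is no fault. The point concerns a selection rule that the article does state.

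**Clustering is the larger problem.** A reader might infer that fixed covariates would deal with the five-area design. They would not: with baseline always included, simulated type I error was still about 0.14 at an intraclass correlation of 0.02 and 0.25 at 0.05, because the analysis ignores areas. This also stands, and it is a separate point.

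**Conclusion.** The point holds in a limited form. The stated rule makes adjustment depend on observed baseline differences, lets the covariate set vary between outcomes, and in most trials would leave the outcome's baseline value out as a covariate.

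Reading a difference as p<0.05, a gap up to about 0.28 SD would stay unadjusted and could shift a follow-up-only comparison by up to 0.14 to 0.20 SD. For continuous outcomes, a cut of 25% to 49% in residual variance is nearly always forgone when clients are independent. At a true effect of 0.3 SD, that is power of about 0.54 to 0.55 instead of about 0.65 to 0.82.

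The sizes rest on the inferred cut-off and on assumed correlations of 0.5 to 0.7. The variance figures are client-level and do not carry over directly to area-level variance or to dichotomous and ordinal outcomes. The criticism of the rule itself needs none of these assumptions. The wording should be changed.

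**What to change.** Replace the conditional rule under Statistical methods with wording such as:

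> The main analysis of each outcome adjusts for its baseline value, together with a short list of prognostic covariates fixed before the outcome data are analysed; the unadjusted analysis is supportive. Baseline characteristics are tabulated by group and area and are not used to select covariates.

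The choice of further covariates belongs to the trial team, on prognostic grounds.

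The cost is one paragraph. Baseline measurement is already planned (Participant timeline, Table 1), so no new data are needed, although the article does not say that every client has every baseline value. There is one small downside: in logistic models, adjustment changes the estimated odds ratio to a conditional one, so the list should be kept short where outcomes are sparse. The change does not deal with clustering by the five randomised areas, which needs its own remedy.

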**Methods:**

Health care units involved in the study are from primary care in Lohja, Southern Finland: home care (191 consented clients), the public healthcare center, and a private community pharmacy. System based risk management theory and action research method was applied to construct the collaborative procedure utilizing each profession’s existing resources in medication risk management of older home care clients. An inventory of clinical measures in usual clinical practice and systematic review of rigorous study designs was utilized in effectiveness study design.

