#### Participant timeline

Selected study period was 2 years with measurements at baseline (in 2015), and at 12 (in 2016) and 24 months (in the end of year 2017).

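### The longitudinal analysis set leaves out randomised clients with no follow-up, although the plan promises intention to treat, and the repeated-measures ANOVA named may not fit the plan's own inclusion rule

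*Protocol article*

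**What the plan says.** All of the analysis wording is in the Statistical methods section of the protocol article.

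- Principle: "Data will be analyzed on an intention to treat principle, including all randomized participants in the group to which they were randomly assigned".
- Longitudinal set: "Participants with baseline measurement and at least one follow-up measurement will be included in longitudinal analysis".
- Continuous outcomes: "Continuous outcomes will be analyzed with analysis of variance or covariance and repeated measures analysis of variance or covariance". The form of the repeated-measures analysis is not specified.
- Dichotomous and ordinal outcomes: logistic and cumulative logistic regression, "using generalized estimating equations to account for the correlation between the repeated measurements".

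The Participant timeline section sets the visits: "Selected study period was 2 years with measurements at baseline (in 2015), and at 12 (in 2016) and 24 months". The Randomization section gives 104 clients in the intervention group and 87 in the control group, and says that controls receive the intervention after the first year. No section gives an expected rate of death or drop-out. The Data monitoring section says only that the research coordinator receives information about drop-outs.

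**The concern.** The principle and the longitudinal set describe the same clients only if nobody is lost before a first follow-up. A client who is randomised, measured at baseline and then lost belongs to the first set and not to the second. Both rules are stated, so this is a conflict in the text and not a detail left to a fuller document.

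The setting makes early loss likely to matter. Clients are home-dwelling, aged 65 or over and in regular home care, and home care staff make the measurements. A client who dies or leaves home care probably leaves the measurement system too. The outcomes include function, physical performance, cognition, depression and nutrition, and decline in these may well precede leaving. The trial is open-label and medication changes are prompted in one arm first, so loss could differ between arms.

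The method for continuous outcomes raises a second question. Classical repeated-measures ANOVA needs every time point. A client seen at baseline and 12 months only would satisfy the plan's inclusion rule and still be deleted. The lost 12-month value would come from the one period in which controls have not yet had the intervention.

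**Working it through.** **Step 1. Compare the sets.**

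| Source | Client with no follow-up | Client with one follow-up | Client with both |
|---|---|---|---|
| Intention-to-treat sentence | in | in | in |
| Longitudinal inclusion rule | out | in | in |
| Repeated-measures ANOVA, classical complete-case form | out | out | in |
| Repeated-measures model that accepts incomplete records | in, if baseline is a response | in | in |
| GEE on observed records | out, unless baseline is a response | in | in |

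The first two rows conflict whatever the method. The third conflicts with the second only if the classical form is meant.

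**Step 2. Number of clients.** The article gives 104 and 87, and 104 + 87 = 191, which agrees with the number of consented clients in the abstract. It states no power, sample size or loss figure that could be reproduced.

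**Step 3. Size under assumed loss.** Let *d* be the yearly loss, taken as permanent and equal in both years. The range of 10% to 20% is an assumption.

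- No follow-up: 191 × *d*
- Both follow-ups: 191 × (1 − *d*)²
- Only the 12-month value: 191 × (1 − *d*) × *d*

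| | *d* = 10% | *d* = 20% |
|---|---|---|
| No follow-up, excluded by the stated rule | 19.1 | 38.2 |
| At least one follow-up | 171.9 | 152.8 |
| Both follow-ups | 154.7 | 122.2 |
| 12-month value only | 17.2 | 30.6 |
| Omitted by a complete-case repeated-measures analysis | 36.3 (19%) | 68.8 (36%) |

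**Step 4. When does the exclusion bias the comparison?** A simulation with no treatment effect used a standard normal outcome, 400,000 clients per arm, and loss following a logistic model in the outcome. It compared the means of the clients who remained.

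| Loss pattern | Absolute bias, SD |
|---|---|
| Same dependence on outcome, same loss (15% or 20% in both arms) | about 0 |
| Same dependence on outcome, loss 10% v 20% | 0.08 |
| Same dependence on outcome, loss 15% v 30% | 0.12 |
| Dependence on outcome in one arm only (four loss settings) | 0.09 to 0.18 |

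Outcome-related loss that is identical in both arms did not bias this comparison. Bias appeared when the amount of loss, or its dependence on the outcome, differed between arms.

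**The case against.** The strongest reply is that the article does not commit to complete-case deletion. It does not say which form of repeated-measures ANOVA is meant, and its inclusion rule makes sense only for a method that accepts incomplete records. That stands, and so the second conflict is stated here as conditional.

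A reader might also infer that the 12-month comparison is necessarily restricted to clients still present at 24 months, after controls have crossed over. The text does not support this. The section lists ordinary ANOVA or ANCOVA alongside the repeated-measures form, and an ANCOVA at 12 months would use every client with a baseline and a 12-month value. The 17 to 31 clients with only a 12-month value would be lost to a complete-case repeated-measures analysis, but not necessarily to the trial.

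A third inference is that loss is known to be informative and the result therefore a comparison of survivors. No section gives a loss rate or a mechanism. Informative loss is plausible in these clients but remains an assumption.

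GEE keeps clients with a single follow-up, and it can be valid when loss depends on covariates in the model. The plan allows baseline values as covariates, but only where the groups differ at baseline.

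Finally, clients with a baseline value alone add little information on the treatment effect, so keeping them may change the estimate less than it changes the label. This is fair. It does not remove the conflict between the two stated rules.

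**Conclusion.** The conflict holds: the section promises analysis of all randomised clients and fixes a longitudinal set that depends on a measurement after randomisation. It also names a method for continuous outcomes that, in its classical form, contradicts that set, and does not say whether this form is meant.

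At an assumed 10-20% permanent loss per year, 19 to 38 of 191 clients fall outside the stated set. A complete-case repeated-measures analysis would omit about 36 to 69. These are counts of clients, not of bias. In the simulation the bias was about 0.08 to 0.18 SD when loss or its dependence on the outcome differed by arm, and near zero otherwise. The documents do not show which applies. The point deserves correction before analysis, but it is not evidence that the trial's comparison is biased.

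**What to change.** Analyse continuous outcomes with a likelihood-based linear mixed model for repeated measures at 0, 12 and 24 months, with the baseline value as one of the responses, using all available measurements from all randomised clients. This keeps clients with a baseline value alone and those with one follow-up. Baseline means need not be constrained equal between groups: five areas were randomised, two against three, and the plan itself anticipates baseline differences.

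If the inclusion rule is kept, call the set modified intention to treat and state which repeated-measures form is used.

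For the GEE outcomes, include baseline values in the model as a matter of course, or multiply impute first. Baseline covariates alone do not bring back clients with no follow-up record, so without imputation the modified label applies there too.

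In either case, report deaths, moves to institutional care and withdrawals by group, and add a sensitivity analysis for non-random loss. The mixed model and standard multiple imputation assume that data are missing at random, and the mixed model does not resolve death, since it treats scores after death as merely unobserved.

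The change needs analysis wording and standard software, with no new outcome measurements. The price is slightly more modelling work and reliance on the missing-at-random assumption, which the sensitivity analysis is there to probe.
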